## Abstract

**Background:**

Presbycusis is characterized by sensorineural hearing loss in both ears at high frequencies, which affects more than half of the older adults by the age of 75 years and is often accompanied by tinnitus and cognitive deterioration. Unfortunately, there are no treatments available to restore hearing loss. Treatment mainly focuses on improving the quality of life and communication with hearing aids. Traditional medicine like Ayurveda also explains ailments of a similar nature as Badhirya and advises using drugs with antiaging and neuroprotective activity for treatment. In Ayurveda, Badhirya and Karnanada (senile deafness with tinnitus) are due to vitiation of Vata Dosha. Treatments such as topical oil pooling (Karnapurana) are usually advised to counter Vata, improve hearing capacity, and reduce tinnitus. Kshirabala Taila, a medicated oil formulation prepared with *Sida cordifolia* Linnaeus, is one of the most preferred oils for topical oil pooling in such conditions, as it has a definitive indication for sensory dysfunctions. Drugs like *Withania somnifera* (L.) Dunal (Ashwagandha) are also used, as they ameliorate neurodegeneration and help to improve cognitive dysfunction.

**Objective:**

We propose an exploratory randomized controlled trial study for evaluating the efficacy of TOPMAC (Topical Oil Pooling with Kshirabala Taila and Supplementation of Ashwagandha Churna) in tinnitus suppression and hearing and cognitive function protection in patients aged 60-75 years with mild to moderate presbycusis.

**Methods:**

A parallel, 2-group, exploratory randomized controlled trial will be conducted in an Indian Ayurvedic research center at its outpatient service. Participants (N=60) with mild to moderate presbycusis will be recruited by screening. Participants will be randomized (computer-generated 1:1) to receive either basic treatment and health education (BTHE) or BTHE+TOPMAC for 24 weeks. The primary objective is to compare the efficacy of TOPMAC with that of BTHE in the protection of hearing function. The secondary objective is to compare the efficacy of TOPMAC with that of BTHE in tinnitus suppression and cognitive function protection.

**Results:**

This project was funded in January 2023. The institutional ethics committees at National Ayurveda Research Institute for Panchakarma (3/1/2020/NARIP/Tech/2036) and Institute for Communicative and Cognitive Neuro Sciences (IEC006) approved this study. The first patient was enrolled in September 2023; 22 participants were enrolled as of August 2024. The data analysis is yet to start, and the results are expected to be published by January 2025.

**Conclusions:**

If this exploratory trial is proven effective, it will steer the setting of a definitive randomized controlled trial to test whether the TOPMAC intervention can be incorporated as a cost-effective integrative approach for managing presbycusis. The Indian government has already launched a National Program for Prevention and Control of Deafness to benefit the deaf population. TOPMAC may later be considered for integration with the national program.

**Trial Registration:**

Clinical Trials Registry India CTRI/2023/04/051485; https://tinyurl.com/2h2hry3n

**International Registered Report Identifier (IRRID):**

DERR1-10.2196/55089

## Introduction

Presbycusis (age-related hearing loss) is characterized by sensorineural hearing loss at high frequencies in both ears, delayed central processing of auditory information, and problems understanding speech in loud environments [1]. It is usually associated with an audiogram that reveals the greatest hearing loss at higher frequencies. It affects over half of the older adults by the age of 75 years and nearly all older than 90 years [2]. Hearing loss is often accompanied by tinnitus. Many extensive population-based longitudinal studies have recommended that presbycusis is independently connected with cognitive deterioration.

The issues and effects of presbycusis are exacerbated in older adults due to additional degenerative processes in the central nervous system, which can lead to loss of neuroplasticity, cognitive ability, and other sensory modes, particularly vision [3]. Age-related hearing loss has an impact on both psychological well-being and physical ability. Some recent studies have established independent associations of hearing loss with driving ability, walking difficulty, social isolation, functional decline, and falls [4]. Social isolation causes emotions of incarceration and anxiety, which reduce higher cognitive performance, potentially increasing the economic and societal burden of age-related hearing loss [5]. The risk factors include age, male sex, diabetes mellitus, hypertension, and hereditary hearing loss [6]. Diabetes or hypertension, if not appropriately controlled, may also cause hearing problems through chronic arteriosclerosis. These are common chronic diseases in the aged population, leading to reduced blood flow in the inner ear [6]. Presbycusis is a serious but primarily neglected condition in India. The Indian government has started the National Program for Prevention and Control of Deafness to benefit the deaf population. The aims of this program include medically rehabilitating deaf persons of all age groups and fortifying the existing intersectoral linkages to maintain the rehabilitation program [7].

Unfortunately, there are no treatments available to restore lost hearing. Research on restoring hearing is a growing scientific field [8]. Treatment in most persons includes suitable hearing aids, but it is a limited solution, with some drawbacks. Studies have shown that people who would benefit from hearing aids are hesitant to use them due to cost, fit and comfort, maintenance, attitude, device factors, fiscal factors, psychosocial/situational factors, ear problems, and appearance. More precisely, these causes include the hearing aid’s ineffectiveness in loud environments, low benefit or low sound quality, and incompatibility with the type of hearing loss. Factors affecting hearing aid fit and comfort include the need for assistance in inserting and removing the hearing aid, feeling uncomfortable, or experiencing adverse effects (eg, rashes, itching) [9]. The treatment of tinnitus is also challenging [10]. Tinnitus should be managed using neurophysiological methods such as tinnitus retraining therapy—a combination of cognitive directive counseling and sound therapy, hearing aids, and white-noise generators. However, this retraining therapy also fails in 30%-40% of the patients [11]. A recent systematic review recommended that incorporating conventional or complementary and alternative therapies for treating mild cognitive impairment will be beneficial [12]. All functions of the nervous system in the human body are represented through Vata in Ayurveda. A subtype of Vata, Prana Vata, is situated in the head and controls intellectual functions, cardiovascular functions, sense organs, psychological activities, respiration, and reflex activities such as sneezing, belching, and deglutition [13]. Since presbycusis is a sensory dysfunction with cognitive decline, it is evident that the Prana Vata is impaired here. Ayurveda mentions similar ailments as Badhirya and Karnanada (senile deafness with tinnitus) [14]. The diseases Badhirya and Karnanada occur in the ears primarily by Vata Dosha vitiation. Topical oil pooling (Karnapurana) is a commonly employed treatment in such conditions, as it does the Vatashamana, improves hearing capacity, and reduces tinnitus. No mechanistic studies show the exact mechanism of action of Karnapurana. However, although histologically, the tympanic membrane is impermeable, a recent study [15] has discovered the possibility of a biological mechanism of active transport through the tympanic membrane to the middle ear. This way, the topically pooled medicine might be absorbed to impart its action in the inner ear. Ayurveda recommends a class of drugs termed as Rasayana, which possess antiaging properties that can be beneficial in these conditions. They can exhibit neuroprotective effects in the inner ear and brain tissue. Kshirabala Taila, a medicated oil prepared with *Sida cordifolia* Linnaeus, is preferred as the drug of choice, as it has definitive indications for sensory dysfunctions [16]. An animal study has also demonstrated that the aqueous root extract of *S. cordifolia* Linn has a neuroprotective effect due to its antioxidative properties and validated the Rasayana claim of *S. cordifolia* Linn in neurodegenerative diseases [17]. *Withania somnifera* (L.) Dunal (Ashwagandha) is another medicine commonly used, as it can regenerate damaged nerve cells and thereby improve nerve function [18]. Recent reviews have shown Ashwagandha as a potent medicine for cognitive function protection [19]. A randomized controlled trial has shown that Ashwagandha effectively enhanced immediate and general memory in individuals with mild cognitive impairment and improved attention, executive function, and information processing speed [20]. The administration of the water extract from Ashwagandha (100 mg/kg/d) with drinking water for 8 months has shown to be safe and showed no toxicity in rats [21]. Ashwagandha may operate as a gamma-aminobutyric acid mimetic, cholinomimetic, and agonist for α-7 nicotinic receptors for cognitive function protection [22]. However, no clinical trials or documented data are available on the efficacy of these drugs for presbycusis treatment, despite being widely used in clinics. The only available data is a case report recommending an Ayurveda treatment protocol to effectively improve hearing mechanisms in presbycusis with no side effects [23].

Hence, we propose an exploratory randomized controlled trial for evaluating the efficacy of TOPMAC (Topical Oil Pooling with Kshirabala Taila and Supplementation of Ashwagandha Churna) in tinnitus suppression and hearing and cognitive function protection in individuals aged 60-75 years with mild to moderate presbycusis and comparing this intervention with basic treatment and health education (BTHE) for presbycusis. BTHE includes treatment for diabetes mellitus, hypertension, and dyslipidemia and counsel related to lifestyle modification and avoiding alcohol and cigarette use. The primary objective is to compare the efficacy of TOPMAC with that of BTHE in the protection of hearing function. The secondary objective is to compare the efficacy of TOPMAC with that of BTHE in tinnitus suppression and cognitive function protection.

## Methods

### Trial Design

This is a multicenter, parallel, 2-group, exploratory, randomized (1:1) controlled trial. The plan of enrollment, interventions, and assessments is given in Table 1.

**Table 1 table1:** Schedule of enrollment, interventions, and assessments for the TOPMAC (Topical Oil Pooling with Kshirabala Taila and Supplementation of Ashwagandha Churna) study.

			Screening		Baseline		Intervention period											End of treatment
Timepoint					Day 1		Day 29		Day 57		Day 85		Day 113		Day 141		Day 169	
	Potential participant identification and screening	✓																
	Provision of participant information sheet	✓																
	Eligibility assessment	✓																
	Informed consent	✓																
**Interventions**																		
	Ashwagandha Churna days 1-168			✓		✓		✓		✓		✓		✓				
	Karnapurana: weeks 1,5,9,13,17,21			✓		✓		✓		✓		✓		✓				
	Basic treatment and health education			✓		✓		✓		✓		✓		✓				
**Assessments**																		
	Demographics			✓														
	Tympanometry	✓																
	Pure tone average	✓								✓						✓		
	Speech recognition threshold	✓								✓						✓		
	Speech discrimination score	✓								✓						✓		
	Laboratory investigations	✓								✓						✓		
	Brainstem Evoked Response Audiometry			✓						✓						✓		
	Tinnitus Functional Index			✓						✓						✓		
	Montreal Cognitive Assessment			✓						✓						✓		
	Drug compliance (%)					✓		✓		✓		✓		✓		✓		
	Concomitant medication					✓		✓		✓		✓		✓		✓		
	Rescue medication					✓		✓		✓		✓		✓		✓		
	Adverse reactions					✓		✓		✓		✓		✓		✓		

### Setting

Likely eligible participants would be identified at the outpatient department of the National Ayurveda Research Institute for Panchakarma (NARIP). They will be sent for screening at the Institute for Communicative and Cognitive Neuro Sciences (ICCONS). NARIP is an Ayurvedic research hospital, and ICCONS is a medical hospital in rural Kerala, India.

### Eligibility Criteria

The intended population is adults aged 60-75 years diagnosed with mild to moderate presbycusis. Pure tone audiometry (PTA) will be performed for octave frequencies between 0.25 and 8 kHz, and the pure tone average will be calculated for 500 Hz, 1 kHz, and 2 kHz. The patients with a pure tone average of 26-55 dB hearing loss will be included. The other eligibility criteria are shown in Textbox 1.

Eligibility criteria.
**Inclusion criteria**
Patients aged 60-75 years diagnosed with mild to moderate presbycusis
**Exclusion criteria**
Conductive hearing loss and abnormal middle earCurrent hearing aid user (>3 months)Patients with features of dementiaUncontrolled hypertension (systolic blood pressure >140 mmHg and diastolic blood pressure >90 mmHg)Uncontrolled diabetes (hemoglobin A_1c_>8%).Patients with very high dyslipidemia (total cholesterol >240 mg/dL, low-density lipoprotein >190 mg/dL, high-density lipoprotein >60 mg/dL, triglycerides >500 mg/dL) National Cholesterol Education Program Adult Treatment Panel III classificationPatients with aspartate amino transferase and alanine amino transferase >2 times the upper normal limitPatients with serum creatinine >the upper limits of the normalHistory of malignancy within 5 yearsHistory of cerebrovascular accident within 1 yearHistory of use of ototoxic, psychiatric, and nervous system drugsHistory of hypersensitivity to the trial drug or any of its ingredientsContinuing addiction to smoking and usage of tobacco in any formIndividuals simultaneously or previously (within 30 days before the investigation starts) participating in a clinical investigation using experimental drugs or devices

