### Interventions

#### Comparator

In BTHE, participants will receive treatment for diabetes mellitus, hypertension, and dyslipidemia and counsel related to lifestyle modification and avoiding alcohol and cigarette use. Advice on optimizing individual acoustic environments is provided, including reducing background noise and engaging in face-to-face conversations to maximize exposure to nonverbal communication cues. Lip reading classes will also be offered. This ancillary care is provided within the scope of this trial.

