#### TOPMAC Intervention

The topical oil pooling will be done on weeks 1, 5, 9, 13, 17, and 21. The preparatory procedure includes temporal region massage with processed gingelly oil (Murchita Tila Taila) followed by sudation therapy. The main therapeutic procedure is to instill 5 mL of Kshirabala Taila in each auditory canal for 15-20 minutes in the morning. The therapy procedure includes massaging the ear base, and after 15-20 minutes, the oil will be wiped with dry cotton. Ashwagandha Churna will be supplemented with a dose of 6 grams at bedtime with 10 mL of cow’s ghee for 24 weeks. Participants in both groups are covered under clinical trial insurance.

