### Sample Size Determination

A previously published report on the administration of topical oil pooling in patients with presbycusis showed that the average hearing level for the frequency of 500 Hz, 1 kHz, and 2 kHz after treatment was 53 dB (for air conduction defect of the right and left ears) [11]. We based our sample size calculation on the assumption that the average hearing level at these 3 frequencies will be 50 dB in the TOPMAC+BTHE group, while it will be 60 dB in the BTHE group. A difference of 10 dB after treatment between both groups has been considered clinically meaningful. With a standard deviation of 12 dB, 80% power, and a confidence interval of 95%, the calculated sample size for each arm is 23. The sample size becomes 28.75, rounded to 30 per arm, adding an attrition rate of 25%. Therefore, 60 participants must be enrolled in the trial (30 in each arm). The attrition rate was based on the clinical experience in treatment compliance. Moreover, in a previous study [25] on Ayurveda interventions among older participants, such attrition had occurred. An interim analysis will be performed after 25% of the participants complete the study duration, and then the reassessment of the attrition rate will be considered along with the original sample size.

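### The lipid exclusion sets an upper limit on HDL (>60 mg/dL) that does not fit its label of very high dyslipidaemia, and does not say whether one or all of its limits exclude

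*Protocol article*

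**What the plan says.** In the protocol article, Methods, Eligibility Criteria (Textbox 1), one exclusion reads "Patients with very high dyslipidemia (total cholesterol >240 mg/dL, low-density lipoprotein >190 mg/dL, high-density lipoprotein >60 mg/dL, triglycerides >500 mg/dL". The criterion names the National Cholesterol Education Program Adult Treatment Panel III classification as its basis but does not reproduce it.

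The four limits are separated only by commas, with no 'any', 'all', 'and' or 'or'. In the same textbox, the blood pressure exclusion joins its systolic and diastolic limits with an explicit 'and'.

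The sections on screening, eligibility confirmation and follow-up assessment, and the laboratory row of Table 1, neither restate nor correct the lipid rule.

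**The concern.** The label says that the criterion keeps out people with severely disturbed lipids. Three of its limits do that by setting a ceiling. The fourth, "high-density lipoprotein >60 mg/dL", sets a ceiling on HDL as well. In general clinical usage a raised HDL is not what the term dyslipidaemia is meant to catch. The article does not say this, and the classification it cites is not reproduced, so the supportable statement is that the direction of this limit does not fit the label and has to be checked against its source.

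This is an operative threshold that a screener must apply, not a detail that an article would normally leave out. Applied as printed, it can turn away people whose other lipid values meet the criterion. On the other reading, it can switch the criterion off for people whose values exceed its other limits. In either case another team could not rebuild the enrolled population from the text, although the trial is meant to prepare a definitive one.

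**Working it through.** **The plan's own figure.** The article computes nothing for the lipid rule. Its only design calculation is the sample size: "With a standard deviation of 12 dB, 80% power, and a confidence interval of 95%, the calculated sample size for each arm is 23". With a difference of 10 dB, n = 2 × (1.96 + 0.84)² × 12² / 10² = 22.6, so 23 per arm, which agrees. No lipid quantity enters it, so this point leaves it unchanged.

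**Inputs from Textbox 1.** Exclusion limits in mg/dL: total cholesterol (TC) >240, LDL >190, HDL >60, triglycerides (TG) >500.

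**The two readings, applied to example screenees (mg/dL).**

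| Screenee | Any one limit excludes | All four must be exceeded |
|---|---|---|
| TC, LDL and TG within limits, HDL 65 | Excluded, on HDL alone | Admitted |
| LDL 250, TG 600, HDL 45 (TC at least 250 + 45 = 295) | Excluded | Admitted, because HDL is not above 60 |

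The first row under 'any one' and the second row under 'all four' both conflict with the label. In each, the HDL entry alone decides the result.

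**Which reading is likelier.** LDL and HDL are both parts of total cholesterol. Under 'all four', LDL >190 with HDL >60 forces TC above 190 + 60 = 250. The limit TC >240 could then never change a decision. A limit with no function is unlikely to be intended, which favours 'any one'. That is also the reading under which HDL alone excludes.

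**Possible size.** The article gives no lipid prevalences. Assumed ranges among screenees, low to high: TC >240, 5% to 20%; LDL >190, 1% to 5%; HDL >60, 5% to 25%; TG >500, 1% to 5%. Treating the four as independent, the share excluded under 'any one' is 1 minus the product of (1 − p).

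- Low, with HDL: 1 − 0.95 × 0.99 × 0.95 × 0.99 = 11.5%. Without HDL: 1 − 0.95 × 0.99 × 0.99 = 6.9%. Difference: 4.7 percentage points.
- High, with HDL: 1 − 0.80 × 0.95 × 0.75 × 0.95 = 45.9%. Without HDL: 1 − 0.80 × 0.95 × 0.95 = 27.8%. Difference: 18.1 percentage points (0.4585 − 0.2780 = 0.1805).

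Independence is a simplification, since TC contains HDL. Without it, the share excluded on HDL alone lies between zero and the HDL prevalence itself, which is at most 25% here.

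Under 'all four', the share excluded cannot exceed that of the rarest limit, 1% to 5% on these assumptions. With independence it is about 0.01% or less (high case: 0.20 × 0.05 × 0.25 × 0.05 = 0.0125%).

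**The case against.** The strongest reply is that comma-separated limits in an exclusion list are ordinarily read as alternatives, that investigators also have procedures and a brochure that are not shown, and that the HDL figure comes from a cited classification that is not reproduced. The first part stands: 'any one' is the likelier reading, and the any/all ambiguity is the lesser half of the point. It does not rescue the HDL entry, because that is the reading under which HDL alone excludes. Naming a classification does not explain why a value above 60 should exclude.

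It is also fair that eligibility is settled before allocation and applied alike to both arms, so the comparison between arms is not biased.

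A reader might infer more than the document supports:

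- **That the rule admits almost everyone to an arm taking ghee.** This rests on the less plausible 'all four' reading. The other exclusions would still apply, and participants are randomised 1:1, so only about half would receive it.
- **That the criterion is a failed safeguard against the ghee.** The intervention section does state "Ashwagandha Churna will be supplemented with a dose of 6 grams at bedtime with 10 mL of cow’s ghee for 24 weeks", and 10 mL × 168 days = 1,680 mL. No section links the lipid exclusion to the ghee, and the total volume by itself shows no harm. Under basic care, which both arms get, "participants will receive treatment for diabetes mellitus, hypertension, and dyslipidemia".
- **That the HDL limit explains slow accrual.** The article reports 22 participants enrolled, of 60 planned, between September 2023 and August 2024. It gives no screening failures or reasons, so the link is conjecture.

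**Conclusion.** The point holds in a limited form. The HDL limit runs in a direction that does not fit the exclusion's label, and the list does not say how its limits combine. Each reading produces at least one decision contrary to the label, and nothing elsewhere in the article corrects it.

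The consequence is confined to who is enrolled and to reproducibility of the population. The document does not fix the size: the increment of about 5 to 18 percentage points under 'any one' rests wholly on the assumed prevalences and on independence. The judgement that the direction is wrong for the label rests on general clinical usage and should be confirmed against the cited classification. The entry should be corrected, but it does not threaten the trial's validity.

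**What to change.** Amend the lipid exclusion in Textbox 1 in two respects:

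1. Reconcile the HDL entry with the purpose of the criterion and with the classification it cites. If it was carried over from a classification table and never intended as an exclusion, remove it. If it was intended, state the reason.
2. State whether exceeding any one limit excludes, or whether all must be exceeded.

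Then check the screening log for decisions already taken that turned on HDL alone, and record how the rule was applied in practice, so that the enrolled population can be described correctly. The final clinical rule is for the sponsor and investigators to settle.

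The cost is a one-line amendment and a log check. No new test is needed. If the HDL entry is removed, slightly more screenees will qualify.
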